### Participants and sampling

2.2.

After a review of literature (41, 42, 47), eligibility criteria for the recruitment of patients include age over 18 years, CABG surgery for the first time, no other concomitant surgery during the CABG surgery, no history of respiratory diseases, no drug and alcohol addiction, no history of seizure, no psychological and cognitive problems, living with a family caregiver (spouse, children, siblings, other relatives) in own home, being literate as ability to read and write in Farsi, having a smartphone and ability to use WhatsApp, and signing the informed consent form to participate in the study.

In addition, inclusion criteria for family caregivers will be those over 18 years of age, being close family members of the patient, living with the patient, being literate as ability to read and write in Farsi, having a smartphone and ability to use WhatsApp, signing the informed consent form to participate in the study, ability to establish effective communication, experience of patient care undergoing the CABG surgery for the first time, and no history of mental health problems. Moreover, reluctance to participate, re-hospitalization, and patient death during the intervention will be exclusion criteria.

The required sample size has been separately estimated according to the study’s variables in the literature review including the QoL of CABG patients (41); cardiac symptoms (43); cardiac self-efficacy (48); medication adherence (49). The largest sample size (35 patients in each group) belongs to medication adherence using the following formula and its parameters:$$\begin{array}{c} N=\frac{{\left(z_{1-\frac{\alpha }{2}}+z_{1-\beta }\right)}^{2}*{\left(s_{1}+s_{2}\right)}^{2}}{{\left(\mu_{1}-\mu_{2}\right)}^{2}}\\ z_{1-\frac{\alpha }{2}}=1.96\;\;\;z_{1-\beta }=1.29 \end{array}$$μ_1_: The mean of the dependent variable in the intervention group.

S_1_: The standard deviation of the dependent variable in the intervention group.

μ_2_: The mean of the dependent variable in the control group.

S_2_: The standard deviation of the dependent variable in the control group.

α: Type I error.

β: Type II error.

Considering 10% attrition, the sample size will be 40 dyads of patients and caregivers in each group.

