Sampling in the present study will be conducted sequentially and the dyads of the patient and family caregiver will be recruited. For the random allocation of the samples to control and intervention groups, a randomized block design of two treatments with quadruple blocks will be used. Second author (AM) will generate the random sequence using https://www.sealedenvelope.com. Sealed envelopes will also be used for concealment. An envelope will then be opened by the third author (RI) for each participant to assign them to the control or intervention group based on the card inside the envelope. The process of the study according to the Consolidated Standards of Reporting Trials (CONSORT) flow diagram has been presented in Figure 1.

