Content of the designed program will be sent by the researcher to the patients and their family caregivers in the intervention group via text message, voice and video call in the form of personal messages using the WhatsApp. Agreements will be made with the participants regarding the sending of the program’s content via the app twice a week in the first 4 weeks of the intervention and then once a week in the second 4 weeks of the intervention. In addition, the patients twice a week will be asked about the presence of cardiac symptoms such as angina, shortness of breath, fatigue, depression, sleep problems and pain at surgery, swelling of the legs, increased heart rate, anxiety and anorexia for adjusting the care program according to their needs. Furthermore, the patients and their family caregivers will be free to share their concerns and questions with the researcher via this app, which facilities the continuity of care and follow up.

The control group will receive routine care during discharge consisting of receiving advice on cardiac symptoms’ management, physical activity, medication management, diet, and visits by the physician based on face-to-face instructions provided by the ward nurse using paper pamphlets.

Due to the nature of the intervention, it is impossible to blind the participants or healthcare providers to the assigned groups. However, attempts will be made to minimize the potential for bias by using objective outcome measures and ensuring that the data analysts will be blinded to the group assignment. The control group and the randomized allocation of participants will help with minimizing selection bias. To address compliance and adherence, we will provide participants with clear instructions on how to use the digital messaging application and encourage them to engage with the program regularly. We also will send regular reminders and prompts to encourage compliance and adherence. In addition, we will monitor the participants’ engagement and adherence throughout the study period and will provide additional support and resources to those struggling to comply with the program.

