### Limitations

3.1.

Recruitment for this study is going to begin in April 2022 and is predicted to continue until August 2023. If any technical problem in the implementation of this research using the WhatsApp is faced, a similar internal messaging app called Eitaa will be used as replacement. In addition, possible challenges associated with the use of a digital messaging application such as disconnection and low internet speed may impact the implementation and effectiveness of the intervention. Furthermore, this study will be conducted in a single hospital due to feasibility issues, which may limit the diversity of the patient population and the generalizability of the results to other healthcare settings.

Although WhatsApp is a user-friendly App and patients and family caregivers will be taught about how to use the apps, potential factors such as technological and health literacy, user compliance, or environmental factors may affect the quality of collected data. The two-month follow-up period after the intervention may provide limited insight into the long-term effects of the transitional care program. Therefore, it is suggested that future research examine the long-term effects of the transitional care program.

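### A single fixed block size of four in an open, single-hospital trial makes allocation more predictable than it needs to be

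*Protocol article*

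**What the plan says.** Section 2.2 (Participants and sampling) of the protocol article describes the allocation: "a randomized block design of two treatments with quadruple blocks will be used". It gives no second or varying block size and no stratification. On enrolment it says "Sampling in the present study will be conducted sequentially", and on concealment "Sealed envelopes will also be used for concealment". One author generates the sequence with a web tool, and a different author opens one envelope for each participant. The target is given as "the sample size will be 40 dyads of patients and caregivers in each group".

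Section 2.3 (Intervention) says that "it is impossible to blind the participants or healthcare providers to the assigned groups"; only the data analysts are to be blinded. Section 3.1 (Limitations) says "this study will be conducted in a single hospital due to feasibility issues". With no strata described, this amounts to one running list.

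Most eligibility criteria in section 2.2 are factual, such as first CABG, no concomitant surgery and living with a caregiver. A few need judgement, notably how well the caregiver can communicate and whether patient and caregiver can use WhatsApp.

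**The concern.** A sealed envelope protects the card inside it. It does not protect against inference from the cards already opened. When every block has four places, two per arm, the fourth allocation always follows from the first three. If the first two are alike, the third and fourth are both known. In an open trial with one list and allocations revealed one by one, the information for this deduction builds up at the site.

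The stake is selection at entry. If the person deciding eligibility can foresee the next arm, a borderline dyad could be declined or delayed depending on that arm. Ability to communicate and to use the application plausibly relates to how well a dyad does in a messaging-based programme. All outcomes are questionnaires completed by patients or caregivers (section 2.4). Selection of this kind could therefore be mistaken for an effect of the programme.

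**Working it through.** **The plan's own figure.** The number of blocks follows from the sample size. Section 2.2 says "The largest sample size (35 patients in each group) belongs to medication adherence" and then "Considering 10% attrition". Dividing, 35 / (1 − 0.10) = 38.9, which rounds up to 39; multiplying, 35 × 1.10 = 38.5, which also rounds up to 39. The stated 40 per group is slightly generous and agrees closely enough. Total: 2 × 40 = 80 dyads, and 80 / 4 = 20 complete blocks. The 35 itself cannot be rebuilt because its means and standard deviations are not given, but nothing below depends on it.

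**Inputs.** Block size 4, two arms, 80 dyads (section 2.2). Allocation of 2:2 within each block is inferred from the equal group sizes. The observer is assumed to know the block size and all earlier allocations.

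**Allocations certain in advance.** A 2:2 block has 6 equally likely orders.
- In 2 of them (AABB, BBAA), the third and fourth allocations are certain: 2 per block.
- In the other 4, only the fourth is certain: 1 per block.
- Expected per block: (2 × 2 + 4 × 1) / 6 = 4/3. Share: (4/3) / 4 = 1/3.
- Over 20 blocks: 20 × 4/3 = 26.7 of 80. The minimum is 20 (one per block, 25%) and the maximum is 40 (two per block, 50%).
- Standard deviation: each block adds a second certain allocation with probability 1/3, so √(20 × 1/3 × 2/3) = 2.1.

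**Best-guess accuracy.** The observer always guesses the arm with more places left in the block.
- Position 1: 1/2.
- Position 2: 2/3.
- Position 3: certain with probability 1/3, otherwise even, so 1/3 × 1 + 2/3 × 1/2 = 2/3.
- Position 4: 1.
- Average: (1/2 + 2/3 + 2/3 + 1) / 4 = 17/24 = 70.8%, against 50% under simple randomisation.

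**What other block schemes would do.** The fixed sizes are enumerated exactly. The varying sizes come from 400 simulated trials of 80 dyads, with an observer who knows the set of possible sizes and all past allocations.

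| Scheme | Certain in advance | Best guess correct |
|---|---|---|
| Fixed 4 (as planned) | 33.3% | 70.8% |
| Fixed 6 | 25.0% | 68.3% |
| Fixed 8 | 20.0% | 66.6% |
| Random 4 or 6 | 5.8% | 69.1% |
| Random 4, 6 or 8 | 2.3% | 67.8% |

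Out of 80 dyads, the certain allocations fall from about 27 to about 5 (0.058 × 80 = 4.6) or about 2 (0.023 × 80 = 1.8). Varying the size removes most of the certainty but little of the guessing advantage, because any balanced scheme tends to swing back towards the arm that is behind.

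**The case against.** The strongest reply is that predictability needs a particular observer, and the article does not show that one exists. It does not say who screens or enrols dyads. It separates sequence generation from envelope opening. That healthcare providers are unblinded does not mean that the person deciding eligibility follows the whole list, and a participant who knows his or her own arm can predict nothing. Sampling is sequential, so an enroller could only decline or delay a dyad, not choose from a pool, and few criteria leave room for discretion. All of this stands, and it limits how far the point can go. Separate roles still do not answer it, because the person opening envelopes sees every past allocation.

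A reader might infer that the envelopes fail and that concealment is broken. The documents do not support that: they show a route, not its use. A reader might also infer that any resulting bias could not be detected or removed. That too goes beyond the text. The outcomes are measured at baseline (section 2.4), so selection on baseline level would tend to show as a group difference and could be adjusted for. Selection on unmeasured traits, such as motivation, would escape, so the protection is partial.

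Nor can the order of consent, baseline questionnaires and envelope opening be called wrong. The article does not state it, the flow diagram was not available for this check, and a condensed article may leave such detail to the full protocol.

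**Conclusion.** The point holds as a design weakness that is cheap to reduce. One fixed block size of four, in an open single-hospital trial with one running list, gives an informed observer on average one third of allocations with certainty and a 71% success rate when guessing.

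This rests on three assumptions: that the quadruple blocks are blocks of four, that they are balanced 2:2, and that the observer knows the size and tracks past allocations. Without that last assumption the figures do not apply. They measure exposure to selection bias and say nothing about whether bias occurred or how large it would be. The sample size is unaffected.

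**What to change.** Generate the list, or its unused part, with block sizes varied at random (for example 4, 6 and 8), and keep the sizes from those who screen and enrol. Because the guessing rate falls only to about 68–69%, varying the sizes is not enough by itself. The protocol should also confirm that each envelope is opened only after eligibility, consent and baseline questionnaires are complete, so that a dyad is committed before its arm is revealed.

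The cost is new envelopes for the unused part of the list, one procedural sentence, and a possible final imbalance if recruitment stops within a block. That imbalance is at most half the last block, so 4 dyads when the largest block is 8.

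Section 3.1 predicts that recruitment will run until August 2023. If it is already complete, the list cannot be changed. The report should then give the fixed block size as a limitation and examine baseline balance between the groups.

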**Figure 1 F1:**
[figure not shown]
The process of the study according to the CONSORT flow diagram.

### Intervention

2.3.

Patients in the intervention group will receive an intervention designed based on the PCC approach, evidence-based practice, and clinical knowledge (Figure 2). It consists of the following aspects:

**Figure 2 F2:**
[figure not shown]
The intervention process.

A thorough literature search will be performed to find and use current guidelines and programs on transitional care for patients undergoing cardiac surgeries to their own homes. This program should cover the areas of self-care activities, medication management, management of cardiac symptoms, dietary regimen, sexual and social activity, physical activity, wound care, control of risk factors, and referral to the primary care provider.

Interviews will be performed with patients willing to participate in the study after being hospitalized and their family caregivers to collect data about daily life activities before the surgery, symptoms, impact of symptoms on daily life, social status, and the need for support after discharge.

Development of a person-centered, post-discharge care program by the research team based on the identified needs with the cooperation of the patient and his/her family caregiver. A panel of experts consisting of the nurse, specialist physician, home care specialist, dietician, social worker, and physiotherapist will assess the program in terms of validity and comprehensiveness. Also, it will be shared with the patients’ primary care providers and their perspectives and suggestions will be sought. All participants will receive the educational content based on their needs in the mentioned areas. Before discharge from the hospital, the patients and their family caregivers will be taught about how to use the WhatsApp on their mobile phones using a two-hour education session via lecture, and active discussions.

Content of the designed program will be sent by the researcher to the patients and their family caregivers in the intervention group via text message, voice and video call in the form of personal messages using the WhatsApp. Agreements will be made with the participants regarding the sending of the program’s content via the app twice a week in the first 4 weeks of the intervention and then once a week in the second 4 weeks of the intervention. In addition, the patients twice a week will be asked about the presence of cardiac symptoms such as angina, shortness of breath, fatigue, depression, sleep problems and pain at surgery, swelling of the legs, increased heart rate, anxiety and anorexia for adjusting the care program according to their needs. Furthermore, the patients and their family caregivers will be free to share their concerns and questions with the researcher via this app, which facilities the continuity of care and follow up.

The control group will receive routine care during discharge consisting of receiving advice on cardiac symptoms’ management, physical activity, medication management, diet, and visits by the physician based on face-to-face instructions provided by the ward nurse using paper pamphlets.

Due to the nature of the intervention, it is impossible to blind the participants or healthcare providers to the assigned groups. However, attempts will be made to minimize the potential for bias by using objective outcome measures and ensuring that the data analysts will be blinded to the group assignment. The control group and the randomized allocation of participants will help with minimizing selection bias. To address compliance and adherence, we will provide participants with clear instructions on how to use the digital messaging application and encourage them to engage with the program regularly. We also will send regular reminders and prompts to encourage compliance and adherence. In addition, we will monitor the participants’ engagement and adherence throughout the study period and will provide additional support and resources to those struggling to comply with the program.

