### Data collection

2.4.

The demographic characteristics questionnaire, Cardiac Self-Efficacy Scale (CSES), MacNew Heart Disease HRQL questionnaire (MNHD-Q), Cardiac Symptom Scale (CSS), and Morisky Medication Adherence Scale will be filled out by the patients. Their caregivers will also fill out the demographic characteristics questionnaire, and Caregiver Burden Scale (CBS). To protect the participants’ confidentiality, the questionnaires will be completed in person at the baseline. All questionnaires, except the demographic questionnaire, will be completed by the participants immediately after the intervention and 2 months after the intervention anonymously and confidentially based on the code assigned to each participant on the WhatsApp.

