#### Cardiac symptom scale (CSS)

2.4.4.

It assesses ten cardiac symptoms of angina, shortness of breath, fatigue, depression, trouble sleeping, pain related to incision, swelling of legs, racing heartbeat, anxiety, and poor appetite. These symptoms are measured in three dimensions of the perception of symptoms (yes-no), evaluation of symptoms (frequency and severity), and response to symptoms (interference with physical activity and the enjoyment of life). A score of zero will be given in case of lack of symptoms for three dimensions. A score of 1 is assigned to the perception of symptoms. The scores of frequency and severity, and interference with physical activity and the enjoyment of life range from 1 to 10, and 0 to 10, respectively (43). The validity and reliability of this questionnaire have been confirmed using the CVI score of 0.9–1 and the Cronbach’s alpha coefficient of 85%–98% in patients undergoing the CABG surgery (55).

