### Data analysis

2.6.

The two-sided primary statistical hypothesis will be tested as follows: transitional care program from hospital to own home using a digital messaging application has an effect on the health outcomes of patients undergoing CABG surgery and their family caregivers.

Data analysis will be conducted using descriptive and inferential statistics through SPSS statistical software version 25. Demographic and outcome data will be summarized as frequencies (percentages) or means (standard deviation) according to the level of measurement. To test the study hypotheses, the dependent variables will be cardiac self-efficacy, QoL, cardiac symptoms, medication adherence, and caregiver burden across three time points as at the baseline, immediately after the intervention, and two months after the intervention. Inferential statistical tests including repeated ANOVA test will be used. *P*-value will be set at *p* < 0.05. Furthermore, we will consider the intention to treat analysis for non-compliance or incomplete adherence (missing outcomes). Sensitivity analyses will be performed to assess the potential impact of non-response bias on our findings.

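### Objective outcome measures are offered as protection against bias in an unblinded trial, but all five outcomes are self-report questionnaires, so that protection does not exist.

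*Protocol article*

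**What the plan says.** Section 2.3 (Intervention) of the protocol article states that "it is impossible to blind the participants or healthcare providers to the assigned groups". It then gives two answers to the resulting bias. One is that "attempts will be made to minimize the potential for bias by using objective outcome measures". The other is to keep the allocation from those who analyse the data. It adds that the control group and randomisation help against selection bias.

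Section 2.6 (Data analysis) lists the outcomes: "the dependent variables will be cardiac self-efficacy, QoL, cardiac symptoms, medication adherence, and caregiver burden across three time points". Section 2.4 (Data collection) says who completes them. The self-efficacy and quality-of-life questionnaires and the "Cardiac Symptom Scale (CSS), and Morisky Medication Adherence Scale will be filled out by the patients"; caregivers complete the burden scale. Baseline is completed in person. The two later rounds are completed "anonymously and confidentially based on the code assigned to each participant on the WhatsApp".

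Section 2.3 delivers the programme to the intervention group as personal WhatsApp messages from the researcher over 8 weeks. As part of it, "the patients twice a week will be asked about the presence of cardiac symptoms such as angina, shortness of breath, fatigue" and seven further symptoms, so that care can be adjusted. Section 2.4.4 describes the Cardiac Symptom Scale (CSS) outcome: "It assesses ten cardiac symptoms of angina, shortness of breath, fatigue, depression, trouble sleeping", and five others.

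**The concern.** When an outcome is self-reported, the respondent is in effect the assessor. If respondents know their allocation, the assessment is unblinded whatever is done at the analysis stage. A protocol can accept this and say so. This one instead tells the reader that the outcomes are objective, which would be a real protection if it were true.

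The risk is a difference in reporting between arms. One arm has had 8 weeks of personal contact with the researcher and the other has had routine discharge advice and pamphlets. A wish to please, or a changed awareness of symptoms, could move answers in one arm only, and the comparison would show this as a treatment effect. The article's conclusion speaks of incorporating the programme into existing care if it proves effective, and that judgement would rest entirely on these scales. The limitations in section 3.1 mention literacy, compliance and environmental factors as threats to data quality, but not unblinded self-report.

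**Working it through.** **1. Is any outcome objective?** From sections 2.4, 2.4.2 to 2.4.6 and 2.6:

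| Outcome | Instrument | Completed by | Form | Objective? |
|---|---|---|---|---|
| Cardiac self-efficacy | CSES | patient | 13 Likert items | no |
| Quality of life | MNHD-Q | patient | 27 Likert items | no |
| Cardiac symptoms | CSS | patient | presence, frequency, severity, interference | no |
| Medication adherence | Morisky | patient | 7 yes/no items, 1 Likert item | no |
| Caregiver burden | CBS | caregiver | 22 Likert items | no |

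The count is 5 of 5 self-reported and 0 of 5 objective. Re-hospitalisation and death appear only as exclusion criteria (section 2.2), and engagement is monitored only to support compliance (section 2.3). Neither is an outcome.

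**2. Where do the arms differ in exposure?** Both follow-up rounds use WhatsApp; baseline does not. The intervention arm receives its programme on WhatsApp, and no such contact is described for controls.

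**3. Overlap with the CSS.** The ten symptoms in the section 2.3 check match the ten CSS symptoms one for one. If the checks run for the full 8 weeks, which the text does not expressly say, there are up to 2 × 8 = 16 checks in the intervention arm and none described for controls. The check asks whether a symptom is present. The CSS scores presence, but also frequency, severity, and interference with activity and enjoyment of life. The overlap is therefore with the yes/no perception dimension of one of the five outcomes.

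**4. The plan's own sample size.** Inputs from section 2.2: 35 per group, 10% attrition, z values 1.96 and 1.29. Inflation gives 35 / 0.9 = 38.9, so 39; the stated 40 is consistent with this. The 35 cannot be rebuilt because no means or SDs are given. Φ(1.29) = 0.901, so the implied power is about 90%.

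**5. Detectable difference with 35 per arm.** For a two-group comparison with a common SD:

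d = √[2 × (1.96 + 1.29)² / 35] = √(21.125 / 35) = 0.777 SD.

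A t-test calculation gives 0.79. (The printed formula squares the sum of the two SDs. Taken literally with equal SDs, it would imply √[4 × 3.25² / 35] = 1.10 SD. What 35 against 35 can detect does not depend on that.)

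**6. Assumed bias against that difference.** The documents give no figure for reporting bias, so 0.2 to 0.3 SD between arms is purely an assumption.

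- Against 0.777: 0.2 / 0.777 = 26%; 0.3 / 0.777 = 39%.
- Against 0.79: 0.2 / 0.79 = 25%; 0.3 / 0.79 = 38%.

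The range is about 25 to 39%.

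**7. The same assumption as a false-positive rate.** With no true effect and bias b in SD units, the chance of a significant result in a simple two-sided 0.05 comparison is 1 − Φ(1.96 − δ) + Φ(−1.96 − δ), with δ = b / √(2/n).

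| b (SD) | n = 35 per arm | n = 40 per arm |
|---|---|---|
| 0.1 | 7% | 7% |
| 0.2 | 13% | 15% |
| 0.3 | 24% | 27% |
| 0.4 | 39% | 43% |
| 0.5 | 55% | 61% |

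These compare with a nominal 5%. They illustrate sensitivity and do not estimate the bias in this trial.

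**The case against.** The article is open about the lack of blinding, so readers are not misled on that. The scales are established instruments, and the authors may have meant validated or standardised when they wrote objective. Symptom monitoring is part of the programme under test, so more contact in that arm is intended. These points stand, but they do not rescue the claim: a validated self-report is still answered by someone who knows the allocation.

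Several stronger readings are tempting and the text does not support them.

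- A reader might infer that follow-up answers go back to the researcher who ran the programme. Section 2.4 names neither the recipient nor the format; a coded link sent through WhatsApp would fit the wording. Only the shared channel is established.
- A reader might infer that data collection differs between arms. Section 2.4 describes one procedure for all participants. What differs is the contact beforehand, and a separate form reduces its influence without removing it.
- A reader might infer that the twice-weekly checks rehearse the CSS itself, or the outcomes generally. They cover symptom presence only and touch one outcome of five.
- A reader might set the assumed bias against a smaller detectable difference and obtain a larger share. That would require lower power than the 90% implied by the z value of 1.29.

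**Conclusion.** The point holds as an error in what the protocol states. Section 2.3 names a safeguard that the outcome list in section 2.6 does not contain: 0 of 5 outcomes are objective. Analyst blinding guards against bias in the analysis and randomisation against bias in selection; neither acts on how unblinded respondents answer.

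That opportunity for differential reporting exists follows from the text. Its direction and size do not. The 25 to 39% figure rests on an assumed bias of 0.2 to 0.3 SD, equal SDs in the two arms, 35 per arm and about 90% power. The count of 16 symptom checks assumes that they continue for all 8 weeks.

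The word anonymous is also inaccurate. Answers carry a participant code and must be linked across three time points, so the data are coded (pseudonymised).

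The design can stand, since unblinded self-report is hard to avoid with this intervention. The claim of objectivity cannot, and conclusions should be limited accordingly.

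**What to change.** 1. In section 2.3, delete the claim that the outcome measures are objective. State that all five outcomes are self-reports by unblinded patients or caregivers, and that analyst blinding protects the analysis only.
2. In section 2.4, describe the follow-up data as coded (pseudonymised) instead of anonymous.
3. Specify that both follow-ups in both arms use the same coded form, separate from the chat that delivers the programme, and state who receives the answers.
4. In the limitations and in the reporting of results, say that benefit on these scales cannot be fully separated from reporting bias. For the CSS, add that the intervention arm was repeatedly asked about the presence of the same symptoms.
5. Optionally, report all-cause re-hospitalisation by randomised arm as a descriptive secondary outcome. Section 2.2 makes re-hospitalisation during the intervention an exclusion criterion, so that use must be reconciled first, and events must be ascertained equally in both arms.

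Items 1, 2 and 4 cost only wording. Item 3 needs a simple form and may slightly lower response. Item 5 needs some ascertainment effort, and with 40 per arm and no event rate given it may say little, which is why it is optional and descriptive.
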